**Molecular/Genetic**
◦ Neurofilament light [18]◦ Genetic modifiers, including *MSH3*, *FAN1*, *MLH1*, *PMS1*, *PMS2*, *MLH3*, *TCERG1*, *GPR161*, *RRM2B*, and *CCDC82* [33]
**Neuroimaging**
◦ Striatal, cortical, and white matter volume [17,37,38]◦ Cortical surface area, folding index, and curvature [17]◦ White matter integrity in corpus callosum and corticostriatal pathways [39]◦ Prefrontal-striatal, motor-striatal, and default mode network resting state functional connectivity [40]◦ Hub organization [41]◦ Network segregation [41]
**Cognitive**
◦ General intelligence [38,42]◦ Cognitive processing speed [42]
**Motor**
Finger tapping variability (increased irregularity in rhythm) [37,43]Grip force fluctuations [37,43]Frequency of repetitive movements [37,43]

## Methods

### Ethics (protocol approvals, consents, blinding, and safety)

Study approval and centralized oversight were provided by the WIRB-Copernicus Group (WCG; formerly WIRB; study number: 1269202; IRB Tracking Number: 20192908). WCG ensures compliance with federal regulations, ethical guidelines, local laws, participant safety, and study integrity. The study was conducted according to the principles expressed in the Declaration of Helsinki. Consent (or assent) procedures vary based on the age range of our participants. Assent is a simplified version of the consent document presented in age-appropriate language:

**Ages 6–7:** The assent form is verbally explained to minor participants, and they will choose whether to provide verbal assent. If verbal assent is provided, it is indicated on the physical consent document by the research team memeber who explained the assent form to the minor participant. A parent or legal guardian reviews and chooses whether to provide full written consent on the participant’s behalf.**Ages 8–11:** Literate participants have the assent form verbally explained to them, read, and decide whether to provide written assent. A parent or guardian then decides whether to provide written consent on their behalf.**Ages 12–17:** Both the participant and their parent or legal guardian review the full consent form with a research team member and decide whether to provide written consent.**Ages 18–30:** Adult participants review the full consent form with a research team member and decide whether to provide written consent on their own behalf.

Collecting predictive genetic data for HD in individuals below 18 years of age raises the risk of confidentiality and privacy breaches, the results of which can have highly negative psychological consequences on those individuals. Thus, a study of this kind warrants commensurate security measures. In accordance, all testing is performed in a double-blind manner and all research team members who interact with participants or their families remain blind to the participant’s genetic status. Those who have previously undergone genetic testing are asked not to disclose their results. Team members responsible for data analysis only have access to de-identified data and do not have any contact with participants or their families. At no point, including after the study’s completion, will any team member have access to both identifying information and genetic status. Genetic results are never shared with participants, their families, medical providers, or anyone with access to identifying information. Additionally, participants are free to withdraw from the study at any time. Data obtained prior to the time of withdrawal are retained, unless the participant or their caregiver specifically requests that all collected data be discarded. To verify that our protocols ascend to the appropriate level of security required to protect the records of all participants giving genetic samples in our study, the ChANGE‐HD study protocols were submitted to several HD patient advocacy groups, including Help4HD International, the Huntington’s Disease Society of America (HDSA), and the Huntington’s Disease Youth Organization (HDYO). All groups have reviewed and endorsed our security measures.

### Design

The ChANGE-HD study employs an accelerated longitudinal design (ALD), which is widely regarded as the gold standard for assessing developmental changes in brain development in children [44]. Instead of a traditional longitudinal design with two necessary time points separated by a specified interval, all visits across all participants are combined to create the largest possible pool of assessments. This complementation across hundreds of participants allows for data to be obtained across a wide range of YTO and allows more flexibility for individuals to participate as they can have their follow-up visits anytime nine months after their previous visit, if desired. This design allows us to combine cross-sectional and longitudinal approaches by recruiting participants across the desired age range. The clinical and imaging protocols are modeled after the ‘Adolescent Brain Cognitive Development’ (ABCD) study, providing a well-established framework for cognitive, behavioral, and MRI assessments in a longitudinal multi-site setting [31]. While the protocol has been designed such that several of the measures are standardized for comparison across the range of 6–30 years-of-age (e.g., NIH Toolbox instruments), other measures, such as the Quantitative-Motor (Q-Motor) require age-correction. For every visit, informed consent is obtained, screening procedures are performed, and, if the participant is of childbearing potential, a pregnancy test is performed. The following assessments are completed at each study visit (Table 2; see S2 Table for more details):

**Table 2 pone.0336088.t002:** Procedures performed at each ChANGE-HD visit.

	Baseline Visit 1	Visit 2	Visit 3	Visit 4
Screening	•	•	•	•
Consent	•	•	•	•
Demographics	•	Review and update if changed		
Vitals	•	•	•	•
Urine pregnancy screen *	•	•	•	•
Blood draw	•	•	•	•
Blood processing	•	•	•	•
Saliva **	•			
Birth history	•	Review and update if not collected previously		
Medical history	•	Review and update if changed		
Family history	•	Review and update if changed		
Medications	•	Review and update if changed		
Behavioral protocol (Self and Proxy)	•	•	•	•
Cognitive protocol	•	•	•	•
Motor protocol	•	•	•	•
MRI	•	•	•	•

* All females of child-bearing potential will be tested for pregnancy; ** Only completed at Visit 1 if blood draw is rejected; Details of all these measures are provided in S2 Table.

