### Participants

At baseline, approximately 450 total participants will be enrolled across all sites. Although annual visits are not required for an ALD design, retention is best with close follow-up, and subjects are asked to return annually. We aim to recruit an even distribution of subjects across age groups, with 225 participants in the range of 6–18 years-old and the remaining participants in the range of 19–30 years-old.

Inclusion criteria:

Between 6–30 years oldFluent in EnglishHave a biological parent or grandparent who has been genetically or clinically diagnosed with HD, indicating that the participant is at risk for HD (determined from participant or family report)Demonstrate an age-appropriate understanding of HD and its risks (If the parents indicate that their child is unaware, we will not enroll the participant until an age-appropriate discussion has occurred)

Exclusion criteria:

A history of medical diagnoses that could potentially confound the study results (e.g., major head trauma, seizures, tumors, or any other major medical illness requiring ongoing care). If an aspect of their medical history obscures their symptoms as being directly attributable to HD (e.g., a concomitant congenital disorder) they are excluded from participation.Have Juvenile-onset HD (JOHD)MRI contraindications. Participants of childbearing potential must undergo a urine pregnancy test before their MRI. If positive, they are excluded from the MRI but may still complete other assessments.Manifestation of overt motor features of HD. This is ascertained by reporting from parents (or participants themselves if they are over 18) during a screening visit. If the participant or the parent reports that they are currently manifesting any motor symptom of HD, the participant is referred to a child or adult neurologist for clinical evaluation. These individuals are also invited to participate in the JOHD study if they were diagnosed with JOHD before the age of 21 (see below).

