### Power analysis and sample size calculation

Based on our findings from the Kids-HD sample, our central hypothesis is that GE participants will demonstrate altered trajectories in general brain size and cognition across YTO. Specifically, we predicted that GE individuals will demonstrate significantly larger brain volume (primary outcome measure) and stronger cognition scores (secondary outcome measures) prior to 20 YTO and significantly smaller brain volume and weaker cognition between 20−0 YTO. Using our updated recruitment target of 1,030 assessments across 450 participants, we estimated at least 90% power to reproduce our previous findings at p = .01 (except for cortical thickness; Table 5). Note that Table 5, which shows the results of our power analysis, includes functional and structural measures, but that our power analysis is primarily based on the structural findings from Kids-HD. Assuming 40% of participants are GE (as in the previous study), we can assume at least 400 visits from 180 unique genetically affected participants. The power analysis used the Kids-HD sample from Neema et al. (2024), and was based on 136 visits from 79 gene-expanded participants. Because the mean number of visits (and hence, statistical information) per participant will be higher in ChANGE-HD, a conservative estimate of the overall increase in statistical information (i.e., log-likelihood statistics) is obtained from the ratio of unique participants, which is 2.278. If the findings from Kids-HD hold, then the expected values of the analogous F statistics (Table 5) will increase by at least 2.278-fold. Standard power calculations using these projected F statistics yield results that exceed the above-claimed minimum statistical power.

**Table 5 pone.0336088.t005:** Tests used for hypotheses and power analysis (from Neema et al., 2024).

		Kids-HD				Change-HD		
**Measures**	**N**	**ndf**	**ddf**	**F**	**p**	**Projected F**	**Projected NCP**	**Power**
General Ability Index**	136	1	87.66	13.50	<0.001	30.78	29.445	0.997
Behavior composite**	135	2	120.27	10.91	<0.001	24.87	47.343	>0.999
PANESS**	128	1	46.12	8.92	0.005	20.34	18.933	0.956
Whole brain*	117	3	62.63	7.79	<0.001	17.76	49.491	>0.999
Cerebrum	117	3	62.55	7.80	<0.001	17.78	49.557	>0.999
Cortical gray matter*	117	1	99.90	12.22	<0.001	27.86	26.593	0.995
Cortical surface area	117	1	95.22	12.17	<0.001	27.75	26.468	0.994
Cortical thickness*	117	1	54.67	2.95	0.091	6.73	5.612	0.406

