
#### Statistical analysis using YTO Models.

We will employ a YTO model, which provides a more detailed representation of disease-related changes (between 50 and 0 YTO) than an age-based analysis [15,16,18,23]. Our statistical analyses are derived from Langbehn et al. [80] and our own work [17] investigating neural and behavioral changes across YTO. This method is based primarily on data from individuals with CAG repeats between 41 and 56 [80] but extrapolation has generalized usefully to CAG repeats extending beyond this range (40, 57–70, etc.) [17]. Because individuals with between 36–39 CAG repeats represent an incomplete penetrance group, they will be excluded from the YTO analysis and will be examined separately in exploratory analyses. Individuals with >70 CAG repeats will also be excluded as they are likely to have already begun showing motor symptoms of HD and are likely classified as patients with JOHD. All hypotheses relate to either systematic group difference between GE and GNE individuals or to differences within the GE group driven by CAG expansion length and age (or years to onset as in the NfL analysis). Our analysis approach will include the following steps: 1) age and sex correction based on the data from healthy controls, 2), estimation of YTO, and 3) YTO modeling with testing for potential additional sex differences and sex by YTO interactions.

For each dependent variable, we apply statistical corrections to separate developmental effects of typical aging from those experienced by GE individuals as part of the disease trajectory. We perform this correction by modeling age and sex effects in GNE controls using a regression that includes within-subject and within-family random effects. The models incorporate both linear and potential non-linear age relationships. Nonlinearity is modeled flexibly via restricted cubic splines (“natural splines”). The degree of non-linearity (up to five degrees of freedom) is determined by choosing the model with the lowest Akaike Information Criterion (AIC), with tied AIC values (≤ 1.0) favoring the simpler model. We also test the model for sex and sex-by-age interactions, which are excluded from the final model if found to be nonsignificant. The fitted values for this model are then subtracted from the dependent value to complete the correction.

Estimation of age of motor symptom onset is calculated using the Langbehn model [80] shown below:

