$$\begin{array}{c} Age\;of\;motor\;symptom\;onset=\text{2}\text{1}.\text{5}\text{4}-(\text{9}.\text{5}\text{5}\text{6}-\text{0}.\text{1}\text{4}\text{6}*CAG) \end{array}$$

YTO is then calculated by simply subtracting participants’ ages (in years) from age of motor symptom onset. (The abbreviation YTO, now established by precedent, stands for a slight misnomer. The value is the number of years from the mean age of onset for those with the given CAG length. It is not the individual’s number of years to onset—which is unknowable—and is slightly different from the individual’s expected years to onset, given that they have reached their current age without already experiencing onset.)

A limitation of this YTO approach is that it can only approximate the relationship between true years to HD onset and the outcome measures. As noted earlier, the YTO calculations are slightly biased estimates of participants’ expected years to onset. Furthermore, a person’s true years to onset has a probability distribution around the CAG-specific average. For concave relationships, such as those we typically expect in the neurodevelopment of brain volumes, substitution of an average value for a probability distribution causes at least slight underestimation of the predicted value that would be obtained from a model based on the true (but unknowable) number of years from onset (Jensen’s inequality).

We assess the relationship between YTO and age- and sex-adjusted outcome measures in GE individuals using an additional mixed effects regression, again including random effects for repeated measures of the same participant and for similarities between participants from the same family. Similar to the GNE model described above, the potentially nonlinear influence of YTO is modeled using restricted cubic splines with degrees-of-freedom chosen by AIC. Sex and sex interactions with YTO are tested and included in the model if significant. The mixed effect models are fitted by maximum likelihood and F-test degrees of freedom are estimated using the Satterthwaite approximation. The summary of the resulting model indicates a p-value for the effect of YTO, which, if significant, indicates a statistically meaningful difference of GE from GNE along the YTO trajectory. Finally, we plot these relationships and their 95% confidence intervals to determine where these differences occur along the trajectory (50−0 YTO)

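### The cognitive and motor models have no term for prior test exposure, so GNE retest gain cancels out of GE scores only if both groups have had similar numbers of earlier visits at similar ages

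*Protocol article*

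**What the plan says.** Under Design, the protocol article states "The following assessments are completed at each study visit", and Table 2 marks the cognitive and motor protocols in full at Visits 1 to 4. Timing is left to the participant: "they can have their follow-up visits anytime nine months after their previous visit, if desired". Under Participants, annual return is requested but not required: "retention is best with close follow-up, and subjects are asked to return annually". Screening recurs: "For every visit, informed consent is obtained, screening procedures are performed". Overt motor features of HD are an exclusion criterion.

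Under Statistical analysis using YTO Models, one correction is applied to every outcome: "We perform this correction by modeling age and sex effects in GNE controls using a regression that includes within-subject and within-family random effects". Its other terms are an age spline, sex and, if significant, sex-by-age. The fitted values are subtracted. The GE stage then models YTO by spline, with sex and sex-by-YTO if significant, "again including random effects for repeated measures of the same participant and for similarities between participants from the same family". The imaging-versus-clinical models carry subject and family effects but drop age and sex. No model has a visit-number or first-versus-repeat term. A significant YTO effect is read as a GE-GNE difference.

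The power section makes cognition a secondary outcome with a directional hypothesis: stronger in GE before 20 YTO, weaker from 20 to 0.

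**The concern.** Brain volume does not improve because someone has been scanned before, but a test score can improve with repetition. The plan uses the same correction for both. A subject random intercept removes stable differences between people. It does not remove a gain within a person from first to later testing.

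In a two-step analysis that gain ends up in the GNE age curve and is carried into every GE score by subtraction. If GE and GNE participants of the same age differ in prior exposure, the remainder appears as a shift along YTO, and the stated model has no way to separate it from a disease effect. The trajectory of cognition on either side of 20 YTO is a named hypothesis. The Discussion would also use a replicated early advantage to caution against early lowering of huntingtin, so the shape of the curve matters as well as its p-value.

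**Working it through.** **1. Repeat testing implied by the plan.** The input is the "updated recruitment target of 1,030 assessments across 450 participants".
- All participants: 1,030 / 450 = 2.29 visits each; repeats (1,030 - 450) / 1,030 = 56%.
- GE: at least 400 visits from 180 people = 2.22 each; repeats 220 / 400 = 55%.
- GNE by subtraction: at most 630 visits from 270 people = 2.33 each; repeats 360 / 630 = 57%.
- Kids-HD pilot: 136 / 79 = 1.72 visits each; repeats 57 / 136 = 42%.

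Retest exposure is thus higher than in the sample being replicated. The 400 is a rounded-down minimum: 40% of 1,030 is 412, which gives 2.29 visits in each group.

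The stated power for the General Ability Index (0.997 in Table 5) reproduces. Projected F = 13.50 x 180/79 = 30.76 (printed 30.78), and power at alpha 0.01 is 0.998 by noncentral chi-square or 0.997 by noncentral F. That figure concerns power and does not bear on this bias.

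**2. When the gain cancels.** To first order, with retest gain g and repeat share p at age a:

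bias(a) = g x [p_GE(a) - p_GNE(a)]

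With the overall shares above and an assumed g of 0.30 SD, bias = 0.30 x (0.55 - 0.571) = -0.006 SD, which is negligible. The overall shares do not settle the matter, because what counts is exposure by age and YTO. Mixed models also weight within-person change, so simulation is needed for size.

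**3. Simulations with no true GE effect.** Retest gain, score correlation and return rates are not in the documents and are assumptions. Onset was taken as 21.54 + exp(9.556 - 0.146 x CAG), because this form reproduces the Introduction's example of 26 YTO for age 8 with CAG 48 and for age 22 with CAG 43.

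*Set A.* 270 GNE, 165 GE, about 2.3 visits each, ICC 0.75, gain 0.15-0.30 SD; bias at 10 YTO:
- Equal return: within 0.005 SD of zero.
- GE below 20 YTO with an extra 20-60% chance of stopping at each follow-up: -0.03 to -0.15 SD.
- GNE aged 18+ with that extra chance: +0.04 to +0.19 SD.

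Simplified reruns of the extreme settings gave about -0.10 to -0.11 SD for the GE case. For the GNE case they gave +0.14 SD at 10 YTO, +0.05 at 20 and about 0 at 30 and 40. The mildest GE setting gave -0.01 SD (standard error 0.009).

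*Set B.* 270 GNE, 180 GE, SD 15, ICC 0.8, gain 0.2 or 0.4 SD from the second test on. Points divided by 15 give SD units.

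| Visits per person, GE / GNE | Bias at 10 YTO, gain 0.2 | Bias at 10 YTO, gain 0.4 | Change from 30 to 10 YTO, gain 0.4: as planned, then with term |
|---|---|---|---|
| 2.29 / 2.29 | -0.02 | +0.01 | -0.12, -0.16 |
| 1.7 / 2.68 | -1.15 | -2.47 | -1.43, +0.06 |
| 2.9 / 1.88 | +1.05 | +2.34 | +1.32, +0.02 |
| 1.4 below 20 YTO, 2.5 above / 2.29 | -1.40 | -2.48 | -2.95, -0.17 |

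Under unequal return, the bias at 10 YTO is 1.05/15 = 0.07 to 2.48/15 = 0.17 SD in size. In the last row there is also +0.48 points (0.03 SD) at 30 YTO, because GE participants above 20 YTO were assumed to return slightly more than GNE.

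**4. Effect on the YTO test at 0.05.** In set B, rejection was 0.067-0.100 with no gain, 0.096-0.152 with gain 0.4 and unequal return, and 0.069-0.103 in those same scenarios with a first-versus-repeat term in both stages. The excess over 0.05 with no gain belongs to the two-step method and is not part of this point.

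**The case against.** **Unequal return is not shown.** Study genotype is never shared with participants or families, contact staff are blind, and for minors a parent or guardian consents. The implied mean visits are close. All of this stands. Some participants may already know their result from earlier testing, but the article does not say how many, or whether they return differently.

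**Motor exclusion.** A reader might infer that repeated screening, by removing people with overt motor features, drives large GE attrition. Under set A's age and CAG assumptions, only about 4% of GE person-time below 20 YTO lies within 5 years of predicted onset, and about 0.06% of all GE person-time lies past it. Exclusion alone is unlikely to produce 20-60% extra stopping.

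**Direction.** A reader might also infer that either imbalance imitates the central cognitive hypothesis. It does not. Fewer GNE adult returns push GE scores up at low YTO and leave 30-40 YTO at about zero, which works against the predicted late deficit and produces no early advantage.

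**Size.** The sampling SD of the estimate at 10 YTO is about 0.2 SD, so even the extreme bias is below one standard error. This stands and limits the weight of the point.

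**The analysis plan may cover it.** The article is condensed and the full plan is not shown. But the article lists the model terms and applies one correction to every outcome, so this is a stated model that can be improved and not simply a detail left out.

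**Conclusion.** The point holds as a conditional weakness of the stated model. Retest gain cancels under equal return. Under markedly unequal return with assumed gains of 0.15-0.30 SD, it leaves roughly 0.03-0.19 SD at low YTO, and the lower end is close to nothing. If GE participants near onset return less, the late deficit is created or exaggerated. If GNE adults return less, it is masked.

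The documents do not support saying that the bias is present, because they give neither retest gains nor return rates by genotype and YTO. The primary MRI volumes are not affected. The exposed outcomes are the secondary cognitive scores, the motor measures, and the clinical side of the imaging-versus-clinical models. The distortion is mainly in the shape of the curve; the added false-positive rate is modest.

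**What to change.** For cognitive and motor outcomes:
- Add a prior-exposure term to the GNE correction model (first versus repeat, or first, second, third or later administration) and subtract its fitted value together with age and sex.
- Test a prior-exposure term in the GE YTO model as well, because GE retest gain may differ from GNE. Without it, only the gain common to both groups is removed.
- Tabulate visits per participant by GE/GNE and YTO band, so that readers can see whether return was unequal.
- Report a first-visit-only sensitivity analysis.

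If the full analysis plan already does this, a sentence in the article is enough.

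The cost is analysis-plan wording and one or two degrees of freedom per model; no new data are needed. In set A the term brought bias to 0.01 SD or less when the gain was the same in both groups, and a rerun showed no loss of precision. Visit number is closely tied to ageing within a person, so separating the two relies partly on the age spread between participants. The first-visit analysis uses 450 of 1,030 assessments (44%), so it will be less precise and should serve as a check only.
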